### Objectives

The primary objective of the trial is to determine the clinical and cost effectiveness of PES/EMDR+TAU relative to TAU in adults with intellectual disabilities.

Secondary objectives are:

To determine whether PES/EMDR leads to improvements in other mental health problems and QoL.To conduct an economic evaluation of PES/EMDR, relative to TAU, with people with intellectual disabilities.To evaluate patient and carer satisfaction with PES/EMDR.To determine whether outcome following treatment with PES/EMDR is related to the complexity of PTSD.

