### Participant timeline

Our participant schedule of events and schedule of outcome assessments is found within table 1.

**Table 1 T1:** Schedule of events and outcome assessments

	Study period							
	Referral/clinic prescreening* (≤12 weeks)	Screening (<4 weeks)	Baseline Week 0	Phase 1 (PES/TAU) Weeks 5–16		Phase 2 (EMDR/TAU) Weeks 17–27		Follow-up Week 60
Week	**≤–12**	**–4**	**0**	**5–15**	**16**	**17–27**	**28**	**60**
Participant and carer								
Clinical history	Y							
Patient information	Y							
Participant								
Consent		Y						
Diagnostic interview		Y						
Diagnostic review		Y						
Concomitant medication		Y		Y	Y	Y	Y	Y
Confirm eligibility		Y						
Randomisation			Y					
Treatment (1–10 sessions for phase 1 and phase 2)				Y	Y	Y	Y	
Adverse events				Y	Y	Y	Y	Y
Subjective Units of Distress Scale (SUDS)				Y	Y	Y	Y	Y
IQ (WASI-II)		Y						
PTSD History (TIF)		Y						
PTSD Diagnosis/Complexity (ITQ-ID)		Y		Y	Y	Y	Y	Y
Self-reported questionnaires*†			Y		Y		Y	Y
Carer								
Adaptive Behaviour Assessment System - III (ABAS-III)		Y						
Carer-reported questionnaires‡			Y		Y		Y	Y
Self-reported questionnaires§			Y		Y		Y	Y
Service/Support Costs (CSRI-ID)			Y	Y		Y		Y
Audio recording	With participants' consent, one treatment session from phase 1 and phase 2 will be recorded with scoring using the EMDR Fidelity Rating Scale							
Interview	In line with qualitative recruitment methods, around 10 each of patients, carers and therapists will be interviewed about their experiences following completion of therapy.							

All visits are anticipated to take place in clinic or community settings, although other scenarios are permissible as required

* Completed assessments must be within 12 weeks of screening

† Patient completed self-reported questionnaires consist of IES-ID, GDS, GAS, PWI-ID

‡ Questionnaires completed by the carer regarding the participant: MPAS-ID, LANTS, ABC.

§ Questionnaires completed by the carer about their own well-being: SF-12, WEMWBS

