#### Assignment of interventions: allocation

Potential participants and carers who fulfil all inclusion and meet no exclusion criteria will be informed of their screening results by local research staff and arrangements will be made for randomisation and treatment visits.

A web-based randomisation and back-up system will be provided by Sealed Envelop (https://sealedenvelope.com) based on a trial minimisation algorithm and randomisation list developed in consultation with a Swansea Trials Unit (STU) statistician. Participants will be assigned 1:1 to either the PES+EMDR group or TAU using IQ, PTSD status and gender as minimisation variables. The randomisation protocol will be implemented by the Trial Manager.

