### Statistical methods for primary and secondary outcomes

#### Quantitative outcomes

The primary outcome will be assessed using an intention-to-treat analysis. Quantitative outcome measures will be analysed by analysis of covariance, adjusting for baseline values of the outcome and any variables used in the randomisation process. Secondary outcomes will be analysed using linear or logistic regression models as appropriate reflecting the distribution of the outcome variable. The treatment effect will be estimated as an adjusted difference between sample means, presented with 95% CIs and p values. A statistical and health economic analysis plan (SHEAP) will be produced and finalised before data lock.

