#### Health economic outcomes

The health economic analysis will consist of a within-trial cost-effectiveness using cost–utility analysis of PES+EMDR versus TAU, assessed from the perspective of the UK NHS and personal social services (PSS) at 14 months follow-up.

Resource use and related costs of developing and delivering the intervention, including therapist training, will be recorded and measured. Due to the variability in the delivery of TAU across sites and participants, a bespoke questionnaire will be completed by research assistants to collect any psychological, psychologically informed or other treatment provided by members of the Learning Disability Team for participants allocated to TAU from patient records.

The costs (NHS, other health providers, social care) of supporting participants through the period of treatment will be collected using the Client Service Receipt Inventory–CSRI: ID version^66 67^ adapted for this trial. Resource use will be valued using the most up to date reference costs; otherwise, estimates from the literature, adjusted for inflation, will be used, as is standard for this tool. The CSRI-ID will be administered at baseline and 14-month follow-up.

Descriptive statistics will be used to summarise resource use, costs and outcomes by study arm. Incremental costs and quality-adjusted life-years (QALYs) will be analysed using appropriate regression methodology adjusting for stratification and minimisation variables. The net benefit framework will be used to assess the cost-effectiveness over a range of values for the QALY.

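### The covariates stated for the cost and QALY regressions do not name baseline cost, although it is collected; the cost comparison stays unbiased on average but loses precision

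*Protocol article*

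**What the plan says.** Under Health economic outcomes, the protocol article gives the adjustment set for both economic endpoints: "Incremental costs and quality-adjusted life-years (QALYs) will be analysed using appropriate regression methodology adjusting for stratification and minimisation variables". The allocation section says that participants are assigned "using IQ, PTSD status and gender as minimisation variables". No stratification factor is named in the article.

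The same health economic section says: "The CSRI-ID will be administered at baseline and 14-month follow-up". Table 1 also marks the CSRI-ID at baseline, so a baseline cost will exist for each participant with a completed form.

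For the clinical outcomes, the Quantitative outcomes section uses a different set, "adjusting for baseline values of the outcome and any variables used in the randomisation process". It adds: "A statistical and health economic analysis plan (SHEAP) will be produced and finalised before data lock".

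Cost-effectiveness is not a side question here. The Objectives section opens: "The primary objective of the trial is to determine the clinical and cost effectiveness of PES/EMDR+TAU relative to TAU".

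On utility, Table 1 names no preference-based measure for the participant. Its footnotes read "Patient completed self-reported questionnaires consist of IES-ID, GDS, GAS, PWI-ID" and "Questionnaires completed by the carer about their own well-being: SF-12, WEMWBS".

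**The concern.** Two parts of one methods section treat the baseline value differently. The clinical models use it. The economic models, as listed, use only the variables that drove allocation, none of which measures prior service use or cost.

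Baseline cost is plausibly a strong predictor of later cost in this population. The trial recruits from hospital and community services, and the introduction describes patients who need specialist services and considerable support and who are at risk of admission. Setting, site and prior service use are not among the minimisation variables named, so allocation does not deliberately balance them.

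At stake is the precision of the incremental cost, and hence of the net benefit. So is the protection of this one trial's estimate against an unlucky split of high-cost participants between the arms.

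**Working it through.** **The plan's own sample size, to fix the number per arm.** Inputs from the Sample size section: effect size 0.65, two-sided α 0.05, power 0.90, four participants per therapist, intracluster correlation 0.02, 25% loss.
- The two-sample t-test needs 50.7, so 51 per arm, or 102 in total. This reproduces the stated 102.
- The design effect is 1 + (4 − 1) × 0.02 = 1.06, and 102 × 1.06 = 108.1. This reproduces the stated 108.
- 108 / 0.75 = 144. This reproduces the stated 144.

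So 108 analysable participants means 54 per arm. The article states no separate figure for the economic analysis, and I use 54 for it too.

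**Size of a chance baseline imbalance.** In SD units of the baseline variable, the difference between arms has standard deviation √(2/n per arm) = √(2/54) = 0.192. Its 95% limit is 1.96 × 0.192 = 0.377. With all 144 analysed (72 per arm), the standard deviation would be √(2/72) = 0.167. Clustering by therapist is ignored here.

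**What carries into the cost difference, and what adjustment gains.** Let ρ be the correlation between baseline and follow-up cost. The documents give no value, so a range is assumed. Without adjustment, the part carried through is ρ × imbalance. With linear adjustment, the standard error is multiplied by √(1 − ρ²).

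| Assumed ρ | Carried at the 95% limit (ρ × 0.377) | SE factor √(1 − ρ²) | SE, unadjusted → adjusted (SD units) |
|---|---|---|---|
| 0.3 | 0.11 SD | 0.95 | 0.192 → 0.184 |
| 0.5 | 0.19 SD | 0.87 | 0.192 → 0.167 |
| 0.7 | 0.26 SD | 0.71 | 0.192 → 0.137 |

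**Simulation check.** 10,000 trials of 54 per arm with no true effect:
- The mean unadjusted difference is about 0 at ρ = 0.5 and at ρ = 0.7, so it is unbiased on average.
- Among trials with a baseline imbalance of 0.3 to 0.5 SD, the unadjusted difference is off by 0.18 SD (ρ = 0.5) or 0.25 SD (ρ = 0.7). The adjusted one is off by about 0.
- The empirical standard deviation of the estimate falls from 0.19 to 0.17 (ρ = 0.5) or 0.14 (ρ = 0.7).

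**QALYs.** The same reasoning applies, and baseline utility is also a direct component of an area-under-the-curve QALY. Its trapezoid weight depends on a schedule that the article does not give for utility: (4/2)/12 = 2/12 year if utility is measured at 0, 4, 8 and 14 months, but (14/2)/12 = 7/12 year if only at 0 and 14 months. With no instrument, schedule or SD stated, I put no QALY figure on the effect.

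**The case against.** The strongest reply is that the sentence is not exclusive. It does not say that nothing else will be adjusted for, it leaves the model form open, and a statistical and health economic analysis plan is promised. A condensed article may properly leave full covariate lists to that plan. The baseline rule for quantitative outcomes also sits under the same parent heading and is compatible with the economic section. This stands to the extent that nothing here is irreversible, and the article does not rule baseline adjustment out. It does not remove the point, because the article goes beyond silence: it states a covariate list for these two endpoints, and that list omits a baseline value already being collected.

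A second reply is that chance imbalance is ordinary sampling error, which a confidence interval already reflects. That is right. A reader might infer that the planned analysis is biased, or that a baseline difference would simply be reported as a treatment effect. The simulation does not support that: over repeated randomisations the unadjusted estimate is centred on the truth. The loss is in precision and in error conditional on the imbalance that this trial happens to have.

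A third reply is that the utility half has little to attach to, since no participant utility measure is named. That also stands. The advice on QALYs has to be worded for whichever measure is used.

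Finally, a reader might infer that no stratification factor exists and that the word should go. A condensed article that names none cannot show this; it refers to a minimisation algorithm and a randomisation list whose details are not shown.

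**Conclusion.** The point holds as a modest improvement to a stated rule. The listed adjustment set omits baseline cost, which is available, and so gives a less precise cost comparison than the data allow, one more exposed to chance imbalance.

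The gain depends on the correlation. It is small at 0.3 (standard error about 5% lower), useful at 0.5 (about 13% lower) and substantial at 0.7 (about 29% lower). These figures rest on assumed correlations, 54 analysable participants per arm and a linear model. The correlation should be read as what remains after IQ, PTSD status and gender are in the model; if those already explain part of the cost, the gain is smaller. Skewed costs may change it further.

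Two stronger conclusions are not supported. A gain in power for the economic comparison cannot be stated, because the article gives no power for costs or net benefit and plans to assess cost-effectiveness over a range of QALY values. Nor can a shift in QALYs be quantified, for the reasons given in the working.

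**What to change.** Before data lock, state in the health economic section and in the statistical and health economic analysis plan that:
- incremental costs are estimated by regression on arm, baseline CSRI-ID cost and the variables used in randomisation;
- incremental QALYs are estimated by regression on arm, the baseline value of whichever utility measure supplies the QALYs, and the same variables;
- net benefit is built from these adjusted estimates.

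This brings the economic models into line with the rule already set for the clinical outcomes. The cost is a short change of wording and one extra covariate per model. It needs no new cost data, since the CSRI-ID is already administered at baseline. For QALYs, the plan must first identify the utility measure and confirm its baseline assessment. Making the change openly before lock avoids the appearance of choosing covariates after the results are known.

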#### Interim and subgroup analyses

No interim analyses are planned. A series of subgroup analyses may be undertaken to determine whether PES+EMDR is more effective in certain participants. This may include completers vs non-completers and PTSD vs complex PTSD.

A complier average causal effect analysis will be considered should the data availability be sufficient to estimate the impact of non-compliance. Compliance will be defined as completing at least 80% of PES/EMDR sessions. A series of subgroup analyses on the primary outcomes will be considered considering differences in the IES-ID scores at 60 weeks for: (a) differing levels of general intellectual functioning, and (b) PTSD versus complex PTSD.

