**Methods:**

This is a two-arm parallel single-blind randomised controlled trial comparing PES-EMDR+TAU to TAU including an internal pilot phase. Outcome data will be captured prior to randomisation, and at 4 (after PES), 8 (after EMDR) and 14 months postrandomisation by masked assessors. 144 adults with intellectual disabilities with a diagnosis of PTSD will be allocated (1:1) randomly using minimisation from National Health Service (NHS) community and inpatients services for adults with intellectual disabilities in England. Participants are eligible to take part in this trial if: (1) they are aged 18 or older, but younger than 66, (2) have a Full Scale IQ<75, (3) meet diagnostic criteria for PTSD and (4) have suffered a major identified trauma at least a year earlier and (5) are able to communicate using English and have capacity to consent to take part in this clinical trial. Participants allocated to the active intervention will receive 10 sessions of PES, followed by up to 15 sessions of EMDR alongside TAU. The active intervention is being delivered by psychologists experienced in working with adults with intellectual disabilities who have received additional intervention training. TAU is likely to include medication, behaviour support plans designed to target challenging behaviour, or non-trauma-focused psychological interventions. The primary outcome is a measure of PTSD symptoms. Secondary outcomes are other mental health problems, including anxiety and depression, challenging behaviour, participant and carer QoL, and carer burden. We are also capturing cost data to allow for a cost–utility analysis. A process evaluation will be completed using data generated from semistructured interviews with a sample of participants, therapists and carers alongside the capture of fidelity and adherence data.

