We have also previously piloted a modified phase 2 EMDR protocol.^46^ The major adaptations^45^ are (1) making the stages, language and outcomes more accessible; (2) not preferring side-to-side finger movements over other forms of bilateral stimulation such as tapping; (3) encouraging creative use of expression (such as techniques from art and narrative therapy/storytelling eg,^47^ and (4) involvement of carers where appropriate to support the patient within and/or between therapy sessions.

The intervention is fully manualised. The PES phase comprises 10 weekly sessions which can be extended if required, while the EMDR phase also comprises 10 sessions but can be extended to 14 sessions if required.

Within each trial site, therapists have been trained to deliver PES/EMDR. Training comprised the standard accredited training (previously known as levels 1 and 2 and currently known either as parts 1–3 or parts 1–4). It followed the standard training curriculum split over two blocks to include a further day on our adapted protocol and a final training day following 4–6 months of supervised practice. It is equivalent to standard EMDR accredited training. In light of experience in the early stages of the trial, and in line with the national EMDR training curriculum, therapists are encouraged to undergo 1 month of supervised practice. For a minority of therapists who had previously been trained to deliver EMDR, only the training in our adapted protocol was delivered. All therapists also undertook training on remote delivery of EMDR, comprising a 1-day workshop and access to remotEMDR software (https://www.remotemdr.com/). Additional refresher training was available for sites that experienced significant delays in starting due to COVID-19. The therapists subsequently have access to supervision sessions via MS Teams in small groups, with additional phone supervision available as needed.

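### Completers versus non-completers is listed as a subgroup for treatment effectiveness, although completion occurs after randomisation and only in the PES/EMDR arm

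*Protocol article*

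**What the plan says.** The section Interim and subgroup analyses gives the purpose of the subgroup work: "A series of subgroup analyses may be undertaken to determine whether PES+EMDR is more effective in certain participants". The next sentence names the candidates: "This may include completers vs non-completers and PTSD vs complex PTSD".

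The same section then turns to compliance: "A complier average causal effect analysis will be considered should the data availability be sufficient to estimate the impact of non-compliance". It defines the term as follows: "Compliance will be defined as completing at least 80% of PES/EMDR sessions". It closes with a second subgroup list, for IES-ID at 60 weeks, which contains only level of intellectual functioning and PTSD versus complex PTSD. The Analysis paragraph of the abstract gives that same shorter list. Completers appear in neither.

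The number of sessions is stated in three places:

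- Abstract, Methods: participants "will receive 10 sessions of PES, followed by up to 15 sessions of EMDR alongside TAU".
- Intervention description: "The PES phase comprises 10 weekly sessions which can be extended if required", and "the EMDR phase also comprises 10 sessions but can be extended to 14 sessions if required".
- Participant timeline, Table 1, treatment row: "Treatment (1–10 sessions for phase 1 and phase 2".

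**The concern.** Asking whether a treatment works better in some participants is a question about effect modification. It needs a factor that can be determined in both arms and that treatment has not influenced. Completing PES/EMDR meets neither condition. TAU participants have no PES/EMDR sessions to complete, and whether someone stays in therapy may depend on severity, complexity, support and early response, all of which may also bear on the 14-month IES-ID score.

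A reported finding that PES+EMDR works in completers but not in non-completers could therefore reflect who stays in therapy rather than what therapy does. The analysis is also feasible, because people who stop treatment are invited to stay in the trial and provide outcomes.

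The secondary concern is that the 80% rule names no total. The CACE analysis is the sound route to the compliance question, so its definition of a complier should be fixed before anyone sees attendance alongside outcome.

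**Working it through.** **1. Which comparisons are possible.** A subgroup effect is active minus TAU within one level of the factor. For completers, that requires the TAU participants who would have completed if offered therapy, and they cannot be identified. Two contrasts remain: completers (or non-completers) against all TAU, and completers against non-completers within the PES/EMDR arm. Neither compares groups formed by randomisation.

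**2. Size of the selection bias.** Let *p* be the proportion not completing and *g* the prognostic advantage, in SD, of those who would complete over those who would not, whatever the treatment. Both are assumptions; the article gives neither. Randomisation gives the TAU arm the same mix, so its mean lies *p* × *g* below that of its would-be completers.

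- Completers versus all TAU: bias = *p* × *g*. With *p* = 0.30 this is 0.30 × 0.3 = 0.09 to 0.30 × 0.5 = 0.15 SD in favour of treatment.
- Non-completers versus all TAU: bias = −(1 − *p*) × *g* = −0.70 × 0.3 = −0.21 to −0.70 × 0.5 = −0.35 SD.
- The two apparent subgroup effects then differ by *g*, that is 0.3 to 0.5 SD, with no true difference in effect.
- Against the design effect size of 0.65, the completer bias is 0.09/0.65 = 14% to 0.15/0.65 = 23%.

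**3. Check at the trial's own size.** The sample size reproduces. A two-sample t-test with effect size 0.65, two-sided α 0.05 and power 0.90 needs 51 per arm, or 102. The design effect is 1 + (4 − 1) × 0.02 = 1.06, and 102 × 1.06 = 108.1, stated as 108. Then 108/0.75 = 144. At 1:1 allocation, 108 analysable outcomes give 54 per arm.

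An unadjusted simulation with 54 per arm, no treatment effect, 60–80% completion and a latent correlation of 0.3–0.5 between completing and a better outcome (all assumed) gave:

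- completers versus all TAU: spurious benefit of 0.11 to 0.32 SD, with 8–30% false positives;
- completers versus non-completers within the active arm: 0.48 to 0.88 SD, with 33–84% false positives;
- correlation zero: about 5% false positives for either contrast.

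At 70% completion and correlation 0.3, the simulated gap is 0.50 SD and the bias against TAU is 0.15 SD, which agrees with 0.30 × 0.50 in step 2. The larger biases come from larger implied gaps. Adjusting for baseline IES-ID and the minimisation variables would remove the part of the gap that those variables explain, but not the rest.

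**4. The 80% rule.**

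- Table 1, and the unextended course in Intervention description: 10 + 10 = 20; 0.8 × 20 = 16.
- Extended EMDR in Intervention description: 10 + 14 = 24; 0.8 × 24 = 19.2, so 20.
- Abstract maximum: 10 + 15 = 25; 0.8 × 25 = 20.

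Someone attending 16 sessions has 16/20 = 80%, 16/24 = 67% or 16/25 = 64%. Attendances of 16 to 19 are compliant against 20 sessions and non-compliant against 24 or 25. No cap is given for extending PES, so the total could be higher still.

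**The case against.** The wording is permissive throughout: the subgroup analyses may be undertaken, may include this item, and the CACE will be considered. The primary analysis is intention-to-treat analysis of covariance, and no main conclusion rests on the completer contrast. The more specific list in the same section omits completers, and the CACE already addresses the underlying question. All of this stands and keeps the severity down. It does not rescue the item, because carrying out what the sentence describes still gives a comparison confounded by selection.

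Every bias figure also depends on assumed completion rates and prognostic gaps. If completion is unrelated to prognosis there is no bias. That stands too, and the figures are illustrations rather than estimates for this trial.

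On session numbers, Table 1 agrees with the unextended course in Intervention description. The outright clash is between EMDR maxima of 14 and 15, and both give a cut-off of 20. A reader might infer that three conflicting counts give three definitions of compliance, but the arithmetic supports only two. The gap between 16 and 20 arises because the rule does not say whether it refers to the standard or the extended course. The denominator might be fixed in the statistical and health economic analysis plan, which is not shown. The disagreement between the article's own sections remains either way.

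**Conclusion.** The completer subgroup should be removed. It treats a post-randomisation event seen in one arm as an effect modifier. Under an assumed 0.3–0.5 SD prognostic gap and 30% non-completion, it would favour treatment in completers by 0.09 to 0.15 SD against all TAU through selection alone. The point is worth fixing but not critical, because the analysis is exploratory and the primary analysis is untouched.

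The session numbers and the compliance denominator are a smaller, secondary matter. The sections need to be reconciled and one denominator stated.

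A reader might go further and infer that the 80% definition is itself an error, or that the CACE must be biased upwards. The document does not support that. A prespecified attendance threshold is a standard definition of compliance. Upward bias arises only if people below the threshold benefit on average; if they gain nothing there is no such bias, and if they worsen it reverses. The article gives no evidence on which of these applies.

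**What to change.** - Delete completers versus non-completers from the first subgroup list in Interim and subgroup analyses. That list then agrees with the abstract and with the second list in the section in omitting completers.
- Address non-compliance only through the randomisation-based CACE already proposed.
- Have the sponsor reconcile the session numbers in the abstract, Intervention description and Table 1. Which number is right is for the sponsor to say.
- State one denominator for the 80% rule in the statistical and health economic analysis plan before data lock, including how extended PES and EMDR courses count.
- Optionally, add a CACE with number of sessions attended as a sensitivity analysis. It should state its assumption that every session adds the same benefit, which is doubtful when treatment comes in two phases and is extended according to need.

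The cost is wording only. Therapists already record attendance after each session, so no new data are needed. The article reports recruitment closed and follow-up under way, so the change is best made now.

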**Analysis:**

The primary outcome will be assessed using an intention-to-treat analysis. Baseline characteristics will be compared between arms to determine whether any potentially influential imbalance occurred. The primary outcome will be analysed by analysis of covariance, adjusting for baseline values of the outcome and any variables used in the randomisation process. Secondary outcomes will be analysed using linear or logistic regression models as appropriate reflecting the distribution of the outcome variable. The treatment effect will be estimated as an adjusted difference between sample means, presented with 95% CIs and p values. A complier average causal effect analysis will be considered should the data availability be sufficient to estimate the impact of non-compliance. A series of subgroup analyses on the primary outcomes will be considered considering differences in the Impact of Event Scale–Intellectual Disabilities scores at 14 months for (1) differing levels of general intellectual functioning and (2) PTSD versus complex PTSD.

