### Interventions

#### Explanation for the choice of comparators

The comparator for the trial is TAU which will be as defined by the therapist and could include any non-trauma-focused intervention. When the trial was designed, trauma-focused interventions were rarely used in the UK with people with intellectual disabilities. They have since become more common, but the restriction was maintained in order to avoid introducing into the trial an element of comparison between two active trauma-focused treatments.

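### Completers versus non-completers is named as an optional subgroup for judging in whom PES+EMDR works better, but completion is known only after randomisation, so the contrast would mix prognosis with treatment effect

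*Protocol article*

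**What the plan says.** All statements are in the protocol article.

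- **Purpose** (Interim and subgroup analyses, first paragraph): "A series of subgroup analyses may be undertaken to determine whether PES+EMDR is more effective in certain participants".
- **Subgroups named there:** "This may include completers vs non-completers and PTSD vs complex PTSD". No definition of a completer follows.
- **Second list** (same section, second paragraph), tied to IES-ID scores at 60 weeks: "a) differing levels of general intellectual functioning, and (b) PTSD versus complex PTSD". Completers are absent. The abstract's Analysis paragraph gives the same two factors: "1) differing levels of general intellectual functioning and (2) PTSD versus complex PTSD".
- **Non-compliance** (same section): "A complier average causal effect analysis will be considered should the data availability be sufficient to estimate the impact of non-compliance". The threshold is "Compliance will be defined as completing at least 80% of PES/EMDR sessions".
- **Who has sessions to complete** (abstract, Methods): "Participants allocated to the active intervention will receive 10 sessions of PES, followed by up to 15 sessions of EMDR alongside TAU". The section Explanation for the choice of comparators says of the control arm: "The comparator for the trial is TAU which will be as defined by the therapist and could include any non-trauma-focused intervention".
- **Primary analysis** (Quantitative outcomes): intention-to-treat, by analysis of covariance on the baseline outcome and the randomisation variables. These are IQ, PTSD status and gender (Assignment of interventions: allocation).

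**The concern.** A subgroup analysis that asks in whom a treatment works better compares the randomised arms within each subgroup and then compares those effects. It therefore needs a grouping variable that is fixed before allocation and can be observed in both arms. IQ and PTSD complexity, both assessed at screening, meet that need. Completion does not, yet the sentence sets it beside PTSD versus complex PTSD as if the two were of one kind.

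People who stay in a long therapy probably differ from those who leave in severity, carer support and early response. If completers have better scores at 14 months, the result looks like a dose-response relation or a responsive subgroup even when the treatment does nothing. If the treatment does work, the same selection inflates the apparent benefit in those who finish.

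The comparison is also feasible. Attendance is logged at every session, and participants who stop treatment are invited to stay and give outcome data. The CACE analysis is itself only to be considered, so the completer contrast could end up as the only compliance result reported.

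**Working it through.** **1. Can the named analysis be built?** There are two possible readings of completer.

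- *Completing PES/EMDR, by the 80% rule.* Only the active arm has PES/EMDR sessions, and TAU has no fixed course, so TAU participants can neither meet nor fail the rule. No randomised contrast exists within either group. What remains is completers against non-completers inside one arm, or each of them against the whole TAU arm. All of these are non-randomised.
- *Completing follow-up.* This exists in both arms but is still settled after randomisation, and those lost to follow-up would lack the 14-month outcome.

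Neither reading gives a baseline subgroup.

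**2. The plan's own sample size, to fix n for the illustration.** The inputs under Sample size are an effect of 0.65 SD, two-sided 0.05, power 0.90, 4 participants per therapist, ICC 0.02 and 25% loss.

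- Two-sample t test: 50.7, so 51 per arm and 102 in total.
- Design effect: 1 + (4 - 1) x 0.02 = 1.06, and 102 x 1.06 = 108.1.
- Loss: 108 / 0.75 = 144.

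The stated 102, 108 and 144 all reproduce. Analysable per arm: 108 / 2 = 54.

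**3. Illustration with no treatment effect.** The protocol gives neither a completion rate p nor a correlation r between the latent propensity to complete and the outcome. Both are assumptions: p from 0.50 to 0.80, r from 0.2 to 0.4. The outcome is in SD units, scored so that higher is better. A participant completes if the latent propensity exceeds c, where P(Z > c) = p and phi is the standard normal density.

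- Mean of completers relative to TAU: r x phi(c) / p
- Mean of non-completers relative to TAU: -r x phi(c) / (1 - p)
- Gap: r x phi(c) / [p(1 - p)]

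For p = 0.65 and r = 0.3, phi(c) = 0.370:

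- Completers: 0.3 x 0.370 / 0.65 = +0.171
- Non-completers: -0.3 x 0.370 / 0.35 = -0.317
- Gap: 0.488 SD

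Simulated null trials with 54 treated participants (about 35 completers and 19 non-completers on average) and an unadjusted two-sided t test at 0.05 reject in about 39-40%. Over the grid:

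| p | r | Gap (SD) | Significant |
|---|---|---|---|
| 0.50 | 0.2 | 0.32 | 21% |
| 0.50 | 0.4 | 0.64 | 67% |
| 0.65 | 0.2 | 0.33 | 20% |
| 0.65 | 0.3 | 0.49 | 39-40% |
| 0.65 | 0.4 | 0.65 | 65% |
| 0.80 | 0.2 | 0.35 | 17% |
| 0.80 | 0.4 | 0.70 | 54% |

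The gap runs from 0.32 to 0.70 SD, set against the trial's target effect of 0.65 SD. The rejection rate runs from about 17% to 67%.

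**4. Completers against all of TAU.** The spurious difference is smaller, from 0.07 SD (p = 0.80, r = 0.2) to 0.32 SD (p = 0.50, r = 0.4).

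**The case against.** Five points can be made for the plan.

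- **The wording is twice conditional.** Subgroup analyses may be undertaken, and may include completers. No model, test or reporting claim is attached. A reader might infer that the analysis is firmly planned and that prognosis will be reported as treatment effect. The text does not support that: the harm arises only if the option is taken up and its result is read as effectiveness.
- **The same section half-corrects itself.** The second list, the one with an outcome and a time point, omits completers, as does the abstract, and a randomisation-based method for non-compliance is named. This stands, and it suggests a loose sentence more than a settled intention. But nothing says that CACE replaces the completer comparison.
- **That completion exists in one arm only is an inference.** It follows from the 80% rule, which the section gives for compliance and not for completers. Under the follow-up reading it would not hold, though the variable would still be post-randomisation.
- **The figures are unadjusted.** The protocol specifies analysis of covariance, which would remove confounding that runs through the baseline outcome, IQ, PTSD status and gender. It would not remove the effect of carer support or early improvement beyond what those covariates carry. The figures apply in full only if r of 0.2-0.4 remains after adjustment.
- **The 17-67% could be misread.** A reader might take it as the false-positive rate of PES/EMDR against TAU. It is the rate of detecting a real prognostic difference within one arm, and it is an error only if that difference is called a treatment effect.

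None of these makes completion a valid subgroup for the stated question.

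**Conclusion.** The point holds in a limited form. The article names, as an option, a subgroup defined by events after randomisation for judging in whom the treatment is more effective. It cannot answer that question under either reading of completer. How far it would mislead depends on a completion rate and a correlation that the protocol does not give, so the illustrated gap and rejection rate show plausible scale and are not predictions.

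A reader might go further and conclude that the trial's main result is at risk. The document does not support that: the primary analysis is by intention to treat, the sample size is untouched, and the two baseline subgroups are sound in kind. The defect sits in an optional secondary analysis, and the section already contains what is needed to replace it. It should be fixed, but it is not critical.

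**What to change.** - Under Interim and subgroup analyses, delete the completers versus non-completers item from the first paragraph, so that both lists in the section and the abstract name the same two baseline factors: intellectual functioning, and PTSD versus complex PTSD.
- Address non-compliance only through the CACE analysis already named there, with its 80% threshold.
- If completers are of interest, describe them in the process evaluation, which already covers adherence and reasons for drop-out. Give no p values and make no statement about effectiveness.

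The cost is one sentence in the protocol and a matching line in the statistical and health economic analysis plan, which is to be finalised before data lock. No data collection, sample size or participant burden changes.
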